### Interventions

This is a naturalistic study. GPs use their professional clinical judgment to recommend a treatment option to the patient. GPs can recommend a non-pharmacological intervention (Active Monitoring Group) or a pharmacological treatment with antidepressants (Medication Group) following their own clinical criteria and experience.

The patients in the Active Monitoring Group receive the usual treatment that the GPs perform when applying active monitoring without a pharmacological treatment. According to the Catalan guideline [13], which has been presented to all the GPs, active monitoring requires a first follow-up visit within the following 15 days. Afterwards, it recommends from six to eight follow-up visits over 10–12 weeks, where the GPs can consider low intensity psychosocial therapies such as counseling, problem-solving techniques or on-line CBT. Also, it recommends structured and supervised exercise programs of moderate intensity. As part of the stepped care model, in case the patient’s condition does not improve, the GP can intensify the treatment and initiate antidepressants.

Adherence to active monitoring is controlled through patient interviews (patients are asked the number of control visits with the GP and the recommendations to deal with depression from their GP). Also, at the end of the study, the GPs will be asked to describe the actions that were taken with patients in the Active Monitoring Group.

The patients in the Medication Group recieve the antidepressants usually prescribed in Spanish primary care at doses usually recommended according to their symptoms and characteristics. The national guidelines recommend initiating a pharmacological treatment with SSRIs (particularly with citalopram, sertraline, paroxetine or fluoxetine) in accordance with the Catalan Health Service’s recommendations following cost-effectiveness criteria [13].

Adherence to antidepressants is monitored through two methods: pharmacy records (computerized pharmacy records that register information about medication including active principle, dose and units supplied in the patient’s clinical history at the time of purchase), and patients’ self-reported adherence (with the 4-item scale developed by Morisky and colleagues [21]).

At the moment of patient inclusion, GPs complete a form that includes the following information: patient allocation (active monitoring or antidepressants) and reasons for the allocation and type and dose of antidepressant prescribed, if any. Withdrawal or changes in treatment and the reasons (initiation of antidepressants or changes in active principle) will be registered in another form. This will allow the evolution of treatment in naturalistic conditions to be monitored.

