### Propensity score calculation

The allocation of patients is done according to the GP’s decisions. Thus, it is expected to have bias, as groups could not be comparable. To minimize the bias resulting from the lack of randomization, we will use a propensity score. First, it will be evaluated where the probability of receiving active monitoring or antidepressants is affected by GP factors (socio-demographic characteristics, job characteristics, training, attitude towards depression, interest on mental health and participation in communication groups) and/or patient factors (socio-demographic characteristics, baseline severity of depression, presence of major depression according to SCID-I criteria, severity of anxiety, comorbid conditions and beliefs about medicines). Second, a logistic regression model will be used to calculate a propensity score. The dependent variable of this model will be the group (active monitoring or antidepressants) and the independent variables will be those that are associated with a higher or lower probability of receiving active monitoring or antidepressants.

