### Incremental cost-effectiveness ratios calculation

Incremental effects and costs between groups will be modelled using generalized linear models. First, different distribution families and link functions will be tested and Akaike and Bayesian information criterion (AIC and BIC) will be used to decide the model that best fits the distribution of the effects (QALYs and severity of depression) and costs. Second, to select adjustment variables, socio-demographic and baseline clinical variables considered to be relevant will be tested in the models using likelihood ratio tests. All the models will be adjusted for gender, age and the propensity score. Difference in costs and effects will be calculated using the final models in each of the imputed databases and combined as per Rubin’s rules [40]. Incremental cost-effectiveness ratios will be calculated by diving the difference in costs between groups by the difference in effects.

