### Sensitivity analyses

At minimum, the following sensitivity analyses will be performed: 1) an analysis from the healthcare perspective; 2) a per protocol analysis; 3) an analysis using the mean average salary instead of the minimum average salary for productivity losses; 4) an analysis not adjusted for the propensity score; 5) an analysis including only the patients that fulfill DSM-IV criteria for MDD.

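### The GPs' recorded reasons for allocation inform neither the propensity score nor any listed sensitivity analysis, and dropping the score cannot reveal confounding that it misses

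*Protocol article*

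**What the plan says.** - **Recording of reasons (Interventions).** The inclusion form captures "patient allocation (active monitoring or antidepressants) and reasons for the allocation and type and dose of antidepressant prescribed". A second form records later changes of treatment. The only use given for this information is: "This will allow the evolution of treatment in naturalistic conditions to be monitored".
- **Expected bias (Propensity score calculation).** The section itself concedes this: "The allocation of patients is done according to the GP’s decisions. Thus, it is expected to have bias, as groups could not be comparable". The Discussion repeats the point for severity and names propensity score techniques as the remedy.
- **Score candidates (same section).** GP factors are "socio-demographic characteristics, job characteristics, training, attitude towards depression, interest on mental health and participation in communication groups". Patient factors are socio-demographics plus "baseline severity of depression, presence of major depression according to SCID-I criteria, severity of anxiety, comorbid conditions and beliefs about medicines". Of these, "the independent variables will be those that are associated with a higher or lower probability of receiving active monitoring or antidepressants".
- **Outcome models (Incremental cost-effectiveness ratios calculation).** "All the models will be adjusted for gender, age and the propensity score". Other socio-demographic and baseline clinical variables are tried and kept or dropped by likelihood ratio tests.
- **Sensitivity analyses.** Five are listed as a minimum: healthcare perspective, per protocol, average instead of minimum salary, "an analysis not adjusted for the propensity score", and patients meeting DSM-IV criteria only.

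**The concern.** The comparison is only as good as the score's hold on what moved GPs to prescribe. The study asks them exactly that, patient by patient and at the time of the decision, and then makes no analytic use of the answers. A prognostic reason that GPs often give, but that no listed candidate represents, stays in the estimated differences in cost and effect.

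Two candidates are visibly absent:

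- **Baseline disability (WHO-DAS).** It plausibly bears on the prescribing decision and on lost productivity, which is a cost component under the societal perspective.
- **Earlier moderate or severe episodes.** The Background reports them as a guideline ground for antidepressants in mild depression, and the participating GPs were trained on the national guidelines.

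No listed sensitivity analysis asks how strong a missed factor would have to be to change the conclusion. Close agreement between the base case and analysis 4 could then be taken for robustness that has not been tested.

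**Working it through.** The document gives no figure for residual confounding, so there is nothing to reproduce. The check has three parts: a comparison of sections, an illustration of what analysis 4 can show, and a range for the bias.

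**1. Sections side by side**

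| Factor | Named score candidate? | Other route into the model |
|---|---|---|
| Baseline severity, SCID-I diagnosis, anxiety, comorbidity, beliefs about medicines | Yes | Likelihood ratio selection for baseline clinical variables |
| Baseline WHO-DAS | No | Only if selected by likelihood ratio test |
| Prior moderate or severe episodes | No | Only if measured and selected |
| Recorded reasons for allocation | No | None stated |

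The Abstract places patient measurements at baseline, six and 12 months. I therefore take a baseline WHO-DAS score to exist; the schedule figure is not available to confirm it.

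**2. What analysis 4 can show**

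This is a simulation with assumed values throughout: 300 patients, 1,000 replicates and a true effect of zero. Allocation depends on severity and on one reason present in 40% of patients. The PHQ-9 outcome depends on severity and, in the first column, on the reason (2 points).

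| Model | Mean bias, reason prognostic | Mean bias, reason not prognostic |
|---|---|---|
| Crude | 2.45 | 1.94 |
| Score dropped; age, sex and severity kept | 0.54 | -0.02 |
| Score without the reason | 0.54 | -0.02 |
| Score including the reason | -0.02 | -0.02 |

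Dropping the score does not return the crude result (0.54 against 2.45). It gives the same answer as the score-adjusted model, because both use the same measured covariates. The two agree whether the shared bias is 0.54 or nil, so their agreement is uninformative about a missed factor. Where the reason is not prognostic, adding it removes no bias and raises the SD of the estimate from 0.57 to 0.60.

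**3. Range for the bias**

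Bias = (imbalance left after adjustment) × (effect of the missed factor on outcome).

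- QALYs, assumed effect 0.05 and imbalance 0.10 to 0.40: 0.10 × 0.05 = 0.005; 0.40 × 0.05 = 0.020.
- Cost, assumed effect EUR 300: 0.10 × 300 = EUR 30; 0.40 × 300 = EUR 120.
- PHQ-9, assumed effect 1 to 3 points and imbalance 0.1 to 0.3: 0.1 × 1 = 0.1; 0.3 × 3 = 0.9 points.

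Standard error of the QALY difference, with 150 per arm (Sample size) and an assumed SD of 0.15: 0.15 × √(2/150) = 0.017 unadjusted. About 0.018 to 0.02 is reasonable after score adjustment. With 0.02, the bias is 0.005/0.02 = 0.25 to 0.020/0.02 = 1 standard error. With 0.018 it is 0.28 to 1.1. A bias of 0.5 standard error lowers the coverage of a 95% interval to about 92%, and 1 standard error to about 83%.

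**The case against.** The case against is substantial, and much of it stands.

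- **The main indications are already candidates.** Severity, SCID-I diagnosis, anxiety, comorbidity, beliefs about medicines and GP attitudes are all listed. A reader might infer that confounding by indication goes unaddressed. The document does not support that; the gap is what these measures miss.
- **Analysis 4 is not crude.** A reader might also infer that dropping the score merely brings back the unadjusted comparison. As written, the analysis removes the score alone. Gender, age and any selected baseline clinical variables remain, and the result is near-crude only if few are selected. Nor does the article present analysis 4 as a test of residual confounding. Showing how far the score moves the estimate is a legitimate use.
- **WHO-DAS may enter through the outcome models.** It may, but entry depends on a likelihood ratio test and is not assured.
- **Analysis 5 helps.** Restricting to confirmed DSM-IV cases limits confounding by diagnosis to some extent. GPs were blind to that diagnosis, however, so it does not capture why they prescribed.
- **A recorded reason need not be a confounder.** It may express preference without prognostic value, and entering raw reasons could nearly separate the groups. Both points stand and shape the remedy.
- **This is a condensed article with an open sensitivity list.** Coding rules for the reasons could sit in a fuller plan. The candidate list and the minimum analyses are nevertheless stated choices and can be judged as such. An open list permits a bias analysis but commits to none.

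**Conclusion.** The point holds in a limited form. The reasons for allocation are collected with no stated analytic use. Baseline WHO-DAS and prior moderate or severe episodes are missing from the named score candidates. None of the five listed analyses probes confounding that the score misses. In a study whose answer depends on adjustment, this leaves avoidable residual bias possible and unquantified.

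That does not show that the planned estimate is biased by any particular amount. The range of 0.25 to 1 standard error rests wholly on assumed values: a 0.05 QALY effect, an SD of 0.15, and 10 to 40 points of imbalance. That imbalance must be what remains after conditioning on the listed factors. The upper end supposes that a large difference survives that adjustment, which nothing in the document establishes. The change is worth making because it is cheap, not because a large error has been demonstrated.

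**What to change.** Before outcomes are examined:

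1. Code the recorded reasons into a short set of categories and tabulate them by group.
2. Add baseline WHO-DAS, and the measured baseline counterpart of each common and plausibly prognostic reason, to the propensity score as forced covariates. They should not depend on an association screen. If prior episodes are available from baseline data, include them; if not, carry them to step 4. Do not enter the raw reasons.
3. Check overlap of the score between groups after these additions.
4. Add a quantitative bias analysis for factors with no measured counterpart. For residual prevalence difference d, QALY effect a, cost effect c and willingness to pay λ, the shift in incremental net benefit is d × (λa − c). Report the combinations that would reverse its sign at stated values of λ.
5. Keep analysis 4 as a descriptive comparison, and say that its agreement with the base case is not evidence against unmeasured confounding.

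The cost is coding about 300 form entries (2 × 150), one further calculation, and a slightly larger propensity model with a small loss of precision. Coding and the bias analysis need no new data collection.

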### Outcomes and participant timeline

The primary outcome of the study is cost-effectiveness, measured in terms of incremental cost per reduction of the severity of depression achieved and in incremental costs per quality adjusted life years (QALYs) gained. Figure 1 shows all the measures administered at each assessment visit as well as the time schedule of patients.

**Figure 1 Fig1:**
[figure not shown]
**Schedule of enrolment, interventions and assessments.** PHQ-9 = Patient Health Questionnaire; CSRI = Client Service Receipt Inventory; BMQ = Beliefs about Medicines Questionnaire; SCID-I = Structured Clinical Interview for DSM Disorders; BIPQ = Brief Illness Perception Questionnaire; WHO-DAS 2.0 = World Health Organization Disability Assessment Schedule; BAI = Beck Anxiety Inventory; MAQ = Medication Adherence Questionnaire.

Costs are collected from a societal perspective. Use of health care resources and lost productivity are assessed using the Client Service Receipt Inventory (CSRI) [22] with a recall period of 12 months at baseline and six months at point two and close-out. We collect information on productivity losses, health tests, hospital care (emergency visits and stays), secondary care (visits to psychologists, psychiatrist and other specialists), primary care (visits to GP and nurse), medication use and social care services (visits to social worker). Information on the use of psychotropic medicines (active principle, dose and units supplied) is also collected from computerized pharmacy records.

The unit costs of public healthcare services are obtained from the Official Bulletin of the Catalan Government. Costs of privately funded services are obtained from published tariffs. The mean price per milligram of active principle is calculated using the prices of the generic versions of all the presentations as reported in the Spanish Vademecum. Productivity losses will be calculated based on the human capital approach using information on the minimum and average daily wage in Spain (INE) [23].

Changes in the severity of depression are assessed using the Patient Health Questionnaire 9-item depression module (PHQ-9) [24-26]. The PHQ-9 is a nine-item scale with items scored from 0 (not at all) to 3 (nearly every day) on nine symptoms of depression. Summed scores range from 0 (no depressive symptoms) to 27 (all symptoms occurring daily). Summed scores of 20 to 27 correspond to severe symptoms; 15 to 19 to moderately severe; 10 to 14 to moderate symptoms; 5 to 9 to mild symptoms; and 0 to 4 to minimal symptoms.

The Spanish version of the EuroQol-5D (EQ-5D) is used to measure health-related quality of life [27-29]. The EQ-5D records self-reported problems in five domains (mobility, selfcare, usual activities, pain/discomfort and anxiety/depression) divided into three levels of severity (no problems, some problems, and extreme problems), thus generating 245 possible health states [30]. Each state corresponds to a single index value referred to as the tariff. Value 1.000 is the best health state and value 0.000 corresponds to being dead. The second part records the subject’s self-assessed health on a Visual Analogue Scale (VAS) on which the best and worst imaginable health states score 100 and 0, respectively. QALYs are calculated by multiplying the utility with the amount of time a patient spent in a particular health state. Linear interpolation is used for transitions between health states.

Clinical diagnosis according to DSM-IV diagnostic criteria was confirmed using the research version of the Structured Clinical Interview for DSM-IV Axis I Disorders (SCID-I) [31]. The modules of mood and anxiety disorders were used. A low concordance between diagnosis of MDD by GPs and SCID-I criteria has been described [9]. It was considered important to check the diagnosis with SCID-I. However, the study was naturalistic so the diagnostic according to DSM-IV criteria was informative and not used as an inclusion criteria. GPs were blind to the DSM-IV diagnosis and patient inclusion was performed according to their usual practice.

Disability was assessed using the 12-item interviewer administered version of the World Health Organization Disability Assessment Schedule (12-item WHO-DAS 2.0). Respondents have to indicate the level of difficulty experienced taking into consideration how they usually do the activity, including the use of any assistive devices and/or the help of a person. In each item, individuals have to estimate the level of disability during the previous month using a 5-point scale (none = 1, mild = 2, moderate = 3, severe = 4, extreme/cannot do = 5). The total score is calculated with a syntax provided by the WHO can range from 0 to 100 with higher scores reflecting greater disability. In the ERASMAP study, the Spanish version demonstrated adequate psychometric properties (Cronbach’s α = 0.89) and evidence of unidimensionality [32-34].

The Beck Anxiety Inventory (BAI) is a twenty-one item self-report inventory that evaluates the severity of anxiety. Each question has four possible answer choices that go from 0 (not at all) to 3 (severely) with total scores ranging from 0 (minimal level of anxiety) to 63 (severe anxiety) [35,36].

Chronic physical conditions were assessed using a “yes” or “no” check-list.

Medication Side effects: Evident side-effects are assessed using a brief check-list considering the most common side-effects of antidepressants. For each side-effect the intensity, frequency and causal relation with antidepressant drugs is assessed.

The Beliefs about Medicine Questionnaire (BMQ) assesses the cognitive representations of medication [37,38]. It has two sections, the BMQ-General and the BMQ-Specific. The BMQ-General evaluates general medication beliefs and comprises two 4-item factors: *General-Harm* (medicines are harmful, addictive or poisonous) and *General-Overuse* (medicines are overused or excessively trusted by doctors). The BMQ-Specific evaluates representations of specific medication prescribed for the patient, in this case antidepressants. This part was only administered to patients on the antidepressants group. The BMQ-Specific comprises two 5-item factors: *Specific-Necessity* (the need of antidepressants) and *Specific-Concerns* (dangers of use of antidepressants).

Sociodemographic characteristics are evaluated at the beginning of the study: age, gender marital status, education and working status.

### Statistical analysis

The analysis will be done according to the intention to treat analysis (all the patients will be included in the analysis in the group to which they were allocated independently of the treatment they finally received.

### Missing data

Missing data patterns will be evaluated to assess if it is plausible that data is missing at random [39]. To minimize bias resulting from the loss of information not following a completely at random reason, missing values will be imputed using multiple imputation by chained equations. The imputation model will include relevant socio-demographic and prognostic variables associated with the drop-outs and outcome variables and variables to be included in the final cost-effectiveness models [40].

### Propensity score calculation

The allocation of patients is done according to the GP’s decisions. Thus, it is expected to have bias, as groups could not be comparable. To minimize the bias resulting from the lack of randomization, we will use a propensity score. First, it will be evaluated where the probability of receiving active monitoring or antidepressants is affected by GP factors (socio-demographic characteristics, job characteristics, training, attitude towards depression, interest on mental health and participation in communication groups) and/or patient factors (socio-demographic characteristics, baseline severity of depression, presence of major depression according to SCID-I criteria, severity of anxiety, comorbid conditions and beliefs about medicines). Second, a logistic regression model will be used to calculate a propensity score. The dependent variable of this model will be the group (active monitoring or antidepressants) and the independent variables will be those that are associated with a higher or lower probability of receiving active monitoring or antidepressants.

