An additional problem regarding active monitoring is the lack of consensus on what is the best strategy for implementation and how to overcome the lack of adherence to recommendations. A study examining the factors associated with GPs’ choice of watchful waiting to care management of depression showed barriers that included the clinicians lack of knowledge on psychotherapy and the lack of availability of mental health professionals for referral [18]. In order to choose watchful waiting, GPs may be able to schedule follow-up appointments with the patient and perform low intensity psychosocial interventions or have available referral services for the patient. However, GPs do not routinely receive training in psychological therapy and the adequate number of follow-up sessions (one within the first 15 days and from six to eight during the 10–12 weeks following the diagnosis [13]) can be unrealistic given the existent burden in primary care. This is illustrated by the study by Hegel and colleagues, where the proportion of patients that received at least one contact with the GP during the first month of watchful waiting was of only 21% [14].

It is still necessary to show whether non-pharmacological interventions in mild-moderate major depression can be a feasible and cost-effective alternative compared to pharmacological interventions in actual practice primary care. The aim of this study is to evaluate the cost-effectiveness of active monitoring in comparison to the use of antidepressants for the treatment of mild to moderate MDD in primary care usual practice in a 12-month non-randomized controlled trial.

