Due to the burden of GPs, their lack of training on brief psychotherapy techniques and the lack of referral services available, a risk exists for active monitoring to become no treatment at all. For example, in a trial considering a one-month watchful waiting period only 21% of the sample had at least one contact with the physician during the first month. To guarantee naturalistic conditions in the present study, GPs received brief training on active monitoring principles. Interventions received by patients in the active monitoring group will be registered to determine what active monitoring really means in Catalan primary care real practice. Yet, non-adherence to antidepressants in our context is high [44,45]. A sensitivity analysis using a per protocol strategy of analysis will be performed to determine the impact of the adherence to the protocol both in the active monitoring and antidepressant groups.

Another limitation could be that the GPs introduce changes to the intervention (e.g. initiate antidepressants for patients in the active monitoring group or change active principle/dose in patients on antidepressants) without filling in the study’s registration. An attempt to minimize this will be made through monthly reminders to the GPs. Also, the patient’s history will be reviewed to gather information on medication.

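### Referral access is said to affect the choice and content of active monitoring, but it is not a listed propensity factor and no model includes centre, so unequal access could bias the comparison

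*Protocol article*

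**What the plan says.** All references are to the protocol article.

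- **Choice of strategy (Background).** A cited study of GPs' decisions found barriers to watchful waiting that included "the clinicians lack of knowledge on psychotherapy and the lack of availability of mental health professionals for referral". The protocol adds in its own voice that, to choose this option, GPs may need enough follow-up appointments and either the ability to give low-intensity therapy themselves or to "have available referral services for the patient".
- **Content of the strategy (Discussion).** Alongside GP workload and limited training, the protocol points to "the lack of referral services available, a risk exists for active monitoring to become no treatment at all".
- **Costs (Outcomes and participant timeline).** Visits to psychologists, psychiatrists and other specialists are counted and costed.
- **Propensity score (Propensity score calculation).** The GP-level candidates are "GP factors (socio-demographic characteristics, job characteristics, training, attitude towards depression, interest on mental health and participation in communication groups". The patient-level candidates are socio-demographic characteristics plus "baseline severity of depression, presence of major depression according to SCID-I criteria, severity of anxiety, comorbid conditions and beliefs about medicines". The selection rule is that "the independent variables will be those that are associated with a higher or lower probability of receiving active monitoring or antidepressants".
- **Cost and effect models (Incremental cost-effectiveness ratios calculation).** "All the models will be adjusted for gender, age and the propensity score". Beyond these, only socio-demographic and baseline clinical variables are to be tested for inclusion.
- **Sensitivity analyses.** None of the five listed involves centre. The list is described as a minimum.

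**The concern.** Allocation is by GP judgement, and the protocol relies on the propensity score to deal with the resulting bias. A score balances only what enters it or what is well represented by what enters it. Here the protocol itself names a factor that bears on allocation and on what one group receives. By its nature that factor also bears on secondary-care costs. It is not among the stated candidates, and centre, the obvious stand-in for it, appears in no model.

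If GPs in better-served centres choose active monitoring more often, the Active Monitoring Group would be credited with the benefit of those services and charged with their cost. Part of both the numerator and the denominator of the ratio would then reflect where patients were seen and not the strategy. The issue is bias in the estimate, which is separate from the effect of clustering on its standard error.

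**Working it through.** **Inputs from the protocol.** 12 centres and 68 GPs (Study setting and GP enrolment); up to five patients per group per GP (Eligibility criteria and recruitment); 150 patients per arm (Sample size). The 150 per arm rests on previous experience, with no stated alpha, power, effect or SD. It cannot be reproduced, and this point does not depend on it.

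**Step 1. Does the recruitment quota already balance the groups within centre?**
- Places: 68 × (5 + 5) = 680.
- Target: 2 × 150 = 300.
- Average per GP: 300 / 68 ≈ 4.4. Average per centre: 300 / 12 = 25.

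At the target size most quotas stay unfilled, so the five-per-group rule does not guarantee balance within GP or within centre.

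**Step 2. Size of the bias if access is unevenly spread.** If access shifts the outcome by γ in both groups, then

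bias = γ × [share with access in active monitoring − share with access in antidepressants].

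The documents give neither quantity, so both are assumed. γ is in residual-SD units.

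| Shares with access | γ = 0.2 | γ = 0.5 |
|---|---|---|
| 50% vs 50% | 0 | 0 |
| 60% vs 40% | 0.2 × 0.2 = 0.04 | 0.5 × 0.2 = 0.10 |
| 70% vs 30% | 0.2 × 0.4 = 0.08 | 0.5 × 0.4 = 0.20 |

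In natural units, assume a difference in shares of 10 to 30 percentage points, with access worth 1 to 2 PHQ-9 points and EUR 200 to 500 of secondary care per patient:
- PHQ-9: 0.1 × 1 = 0.1 to 0.3 × 2 = 0.6 points.
- Costs: 0.1 × 200 = EUR 20 to 0.3 × 500 = EUR 150.

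**Step 3. Does a centre term remove it?** A simulation used 12 centres of 25 patients, access in 6 of them, one measured confounder adjusted for throughout, no true treatment effect, and 3,000 runs per setting.

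| Shares, γ | Bias without centre | False-positive rate without centre | Bias with centre | False-positive rate with centre |
|---|---|---|---|---|
| 50/50, 0.2 | 0.002 | 4.7% | 0.001 | 4.9% |
| 50/50, 0.5 | −0.003 | 5.3% | −0.003 | 5.6% |
| 60/40, 0.2 | 0.039 | 5.9% | −0.001 | 4.6% |
| 60/40, 0.5 | 0.096 | 12.7% | −0.004 | 5.3% |
| 70/30, 0.2 | 0.079 | 9.8% | −0.001 | 4.2% |
| 70/30, 0.5 | 0.196 | 36.5% | −0.003 | 5.4% |

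The simulated bias agrees with the formula. Centre was entered as fixed terms. A random effect uses some between-centre information and so may remove somewhat less.

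**The case against.** A reader might infer that centre differences do confound this study's costs and effects. The documents do not support that, for four reasons.

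- **No difference in access is shown.** Nothing says that referral access varies between the 12 centres or between the groups. The barrier in the Background comes from a cited study, and the Discussion describes a general shortage. The Discussion also places all centres in one health area, which may mean similar access. It mentions this as a limit on representativeness, however, and not as evidence of equal access. This objection stands, and it makes the point conditional.
- **The Discussion speaks of active monitoring only.** If access changes outcomes in that group alone, it describes which version of the treatment was given. The comparison would then be unbiased on this account for the patients who actually received active monitoring. The formula above assumes the same effect in both groups, and a centre main effect would not capture an interaction. This stands in part. On the cost side, specialist visits are counted in both groups, so an effect of access in both is at least possible.
- **Job characteristics is undefined.** The GP questionnaire is not shown, and its items on job characteristics or training might carry some of this information. It is therefore too strong to say that referral access cannot enter the score. What can be said is that it is not named.
- **An article condenses a fuller plan.** That would excuse silence. Here the article does state the candidate domains, the fixed covariates and the pool of optional ones, and the point concerns those stated choices.

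There is also a fair objection to a heavy remedy. If centre drives allocation but not outcome, conditioning on it inflates the variance and can amplify residual confounding by unmeasured severity.

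**Conclusion.** The point holds as a conditional weakness in the stated adjustment set. The protocol identifies referral access as influencing both the choice and the content of active monitoring, yet neither it nor centre is named among the propensity factors or the model covariates. The recruitment quota does not close the gap at the planned size. Any between-centre difference in access that is unequally spread over the groups can therefore bias the cost and effect differences.

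The size is unknown. The range of 0.04 to 0.20 SD, or 0.1 to 0.6 PHQ-9 points and EUR 20 to 150, rests wholly on assumed shares and effects, and its top end needs the upper assumptions to hold together. The bias is zero if access does not differ between the groups. The change is worth making because it is cheap and tests the matter directly, not because confounding has been shown.

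**What to change.** 1. In the section on incremental cost-effectiveness ratios, add primary care centre to the cost, QALY and PHQ-9 models, as a random effect or as fixed terms where the data support them.
2. In the propensity score section, add centre to the list of candidates.
3. Report the number of patients in each group at each centre.
4. Present the results with and without centre, and say in advance which is the main result.

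**Cost.** A few lines in the analysis plan and no new data, since the recruiting centre should be known for every patient. Fixed terms use up to 12 − 1 = 11 degrees of freedom out of about 300 patients, with some loss of precision. If centre turns out to drive allocation but not outcome, the variance may be inflated. Showing both sets of results lets the reader see this. Forcing all 12 levels into every model, or merging centres thought to be similar, is more than the problem calls for.
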